### 7.1. Modules 1-2-3 Plan Analyses

Descriptive analyses will be performed to establish frequencies, means and standard deviations across key categorical and continuous variables of interest. Bivariate and multivariate analyses, including analysis of variance, *t*-tests and correlations will examine the relationship between caregiver and care recipient characteristics (e.g., age, gender, ethnicity, illness type, type of caregiving relationship, etc.), willingness and motivations to provide care, and key caregiver and care recipient outcomes (e.g., caregiver burden, depression, relationship satisfaction etc.).

Relevant, theoretically informed tests of mediation and moderation will be applied prior to conducting hierarchical multivariate regression analyses to assess the extent of outcome variance explained by the IV set, for example moderating or mediating the effects of: (1) relationship quality, gender, or perceived choice in assuming the caregiver role; (2) willingness to care and relationship quality of the caregiving dyad; (3) interpersonal processes and type of relationship between caregiver and care recipient.

Changes over time in IVs or caregiving outcomes will be analysed in the longitudinal data set using repeated measures tests (*t*-tests, ANOVA, MANOVA).

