## Abstract

Informal caregivers are those who provide unpaid care to a relative or friend with a chronic illness, disability or other long-lasting health or care need. Providing informal care in the context of chronic health conditions presents a significant global challenge. Examination of the determinants of informal caregivers’ behaviour, especially in terms of motivations and willingness to provide/receive care, is crucial to understanding the nature of caregiver and care recipient experiences. A large group of international researchers have co-operated to execute the ENTWINE iCohort-a multinational, transdisciplinary, longitudinal study incorporating intensive methods to examine caregiver experiences in the context of chronic health conditions. The aim of ENTWINE-iCohort is to investigate the broad spectrum of factors, i.e., cultural, personal, geographical, relational, psychological, and economic that may affect motivations, willingness to provide or receive care, among diverse groups of informal caregivers and their care recipients, in different countries that have different care systems. Study questionnaires will be disseminated on-line in nine countries: Germany, Greece, Ireland, Italy, Israel, the Netherlands, Poland, Sweden, and the UK. Cross-sectional and longitudinal multivariate analysis, including intensive longitudinal and dyadic data analysis will be applied to examine the relative contribution of the above factors to caregiver or care recipient wellbeing.

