### 1.2. Secondary Objectives

To conduct a full examination of the:

Determinants of, and cultural differences in, motivations and willingness to provide care with specific attention paid to the contribution of personal values and meanings attached to illness and caregiving and their impact on caregiver outcomes,

Personal and geographical barriers and facilitators of caregiving with specific attention paid to the contribution of caregivers’ personality traits and geographic distance from the care recipient upon willingness to care and caregiver outcomes,

Diversity in experiences of caregiver—care recipient dyads, with specific attention paid to the characteristics of the dyads, interpersonal processes, willingness to provide and receive care and individual and relational outcomes.

Patterns of and differences across countries in informal care costs, as well as the preferences for, and use of, formal versus informal caregiving, and the personal and contextual influences thereon.

Characteristic of access to, use of and challenges of household-based migrant care work and how this supports informal caregiving

Each of these objectives is addressed in detail by one early stage researcher (five in total), each under supervision of two senior academics, and with oversight held by a Work Package Lead and ENTWINE management team.

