## 5. Sample Size Calculation

Whilst each specific ESR project has its own objectives (as described above), three are addressing those in relation to the primary outcomes of willingness and motivations to care. Given the number of variables to be assessed (see Measures, approximately 30 variables will be used in total) it is our intention to recruit CGs to the case: variable ratio of 10:1, i.e., 300 CGs per country. For CRs, who are assessed on fewer variables, we expect at least 150 participants per country—anticipating that at least 50% of our sample of 300 CGs per country will identify an eligible care recipient (based on our previous research). Analyses will be appropriate to the attained sample size on study completion in order to achieve satisfactory statistical power.

The a priori sample size calculation was informed by previous research. Achieving 90% power to detect a medium sized association/ explained variance R^2^ = 0.25, with entry of up to 10 independent variables (randomly selected variables dependent on prior analyses) and willingness to care (measured as a continuous variable) in a multivariate regression analysis with an alpha of 5% (G*Power 3.1, [31]).

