## 6. Measures

Table 1 presents all measures used within the ENTWINE iCohort survey, with a brief description of the concept addressed, timings of use, and whether they reflect a key outcome measure (DV) or an IV/potential mediator or moderator variable. Wherever possible, validated instruments were employed, and short-form assessments were preferable where available in order to reduce participant burden.

Measures that are not validated and available in the required language will be translated into the appropriate languages using accredited translators who will be native speakers of the target languages and fluent in English. Translations will be checked for compatibility with the original version in a process of back translation, also performed by persons who will be native in the foreign language and fluent in the English language, to ensure that none of the original meaning is lost. For each language, a potential research consultant/reviewer will be identified to ensure that any discrepancies between the forward and back translations can be resolved appropriately by discussion with the translators. All translations will be coordinated by one project partner to ensure consistency. Piloting in each country shall enable identification of any semantic inconsistencies.

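### Cultural differences in willingness and motivation are an objective, but the plan names only observed-score methods and no check that scores are comparable across languages

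*Protocol article*

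**What the plan says.** - **Objective.** Section 1.2 includes "Determinants of, and cultural differences in, motivations and willingness to provide care". It is one clause of the first of five secondary objectives. The Abstract states: "Study questionnaires will be disseminated on-line in nine countries".
- **Methods.** Section 7.1 says: "Bivariate and multivariate analyses, including analysis of variance, *t*-tests and correlations will examine the relationship". The sentence goes on to caregiver and care recipient characteristics, given as an open list of examples that includes ethnicity but not country or language, and relates them to willingness, motivations and outcomes. Mediation and moderation tests and hierarchical regression follow. No latent-variable method is named.
- **Scales.** In Table 1, the Willingness to Care Scale has 30 items scored 1 to 5 over emotional, instrumental and nursing tasks. The motivation scale is also scored 1 to 5. Both are in the core module, so every caregiver receives them.
- **Assumption checks.** Section 7 gives one list for all analyses: multicollinearity, singularity, normality, linearity and homoscedasticity.
- **Translation.** Under section 6, only measures with no validated version in a language are translated. Safeguards are accredited translators, back translation, a reviewer for each language, one coordinating partner and piloting: "Piloting in each country shall enable identification of any semantic inconsistencies".
- **Size.** Section 5 sets a "case: variable ratio of 10:1, i.e., 300 CGs per country".

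**The concern.** A test on observed scores has as its null hypothesis that the observed country means are equal. That is the same as equal willingness only if each item has the same intercept in every language version. Back translation and piloting check that the wording carries the same meaning. They do not test whether two equally willing respondents, in two languages, choose the same point on a five-point scale. Prior validation of a version within one language does not settle this either.

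If item intercepts differ, a comparison of country means can credit a property of the questionnaire to culture. The article says it wants its findings to inform culturally relevant policy and practice, so such an error would have consequences. A larger sample makes it worse, because the same fixed shift is detected more often.

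**Working it through.** **The plan's own figure.** Section 5 says "approximately 30 variables will be used in total" and applies a 10:1 ratio: 10 × 30 = 300 caregivers per country. This reproduces. It does not rest on any between-country contrast, and this point does not change it.

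**Inputs from the article.** Nine countries; n = 300 per country; alpha 5%. Thirty willingness items over three task types suggest subscales of about 10 items (assumed equal).

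**Assumptions not in the article.** Standardised loading 0.7; true willingness equal in all countries; item-intercept shifts drawn independently for each country and item with SD s = 0.1, 0.2 or 0.3 item SD; country means compared by one-way ANOVA on the mean item score.

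**Step 1: variance of a 10-item mean within a country.** 0.7² + (1 − 0.7²)/10 = 0.49 + 0.051 = 0.541.

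**Step 2: spurious between-country SD, τ, in units of the scale SD.** If k of 10 items shift, τ² = (k·s²/100)/0.541.
- All 10 items: τ = 0.043, 0.086, 0.129 for s = 0.1, 0.2, 0.3.
- Three items: τ = 0.024, 0.047, 0.071.

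**Step 3: rejection rate.** The critical value of F(8, 2691) at 5% is 1.942. With random shifts in all nine countries, the ANOVA statistic is distributed as (1 + nτ²) times a central F. The rejection rate is therefore P[F > 1.942/(1 + 300τ²)], with 1 + 300τ² = 1.55, 3.22 and 5.99. Where only seven countries shift (for example, if the two English-speaking countries use an untranslated version), the noncentral F is averaged over simulated shifts.

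| Scenario, 300 per country | s = 0 | s = 0.1 | s = 0.2 | s = 0.3 |
|---|---|---|---|---|
| 3 of 10 items, seven countries | 5% | 9% | 25% | 51% |
| All 10 items, nine countries | 5% | 27% | 78% | 96% |
| 30-item total, all items, nine countries | 5% | 11% | 37% | 69% |

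The third row uses 0.49 + 0.51/30 = 0.507 as the within-country variance. Independent shifts average out over more items, so the effect is smaller.

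**Attained sample.** The study status paragraph gives 1834 completers, of whom 1120 completed in full. An even split, counting all of them as caregivers (neither is stated), gives 1834/9 ≈ 204 and 1120/9 ≈ 124 per country. For three items in seven countries, rejection is 8%, 18%, 37% at 204 and 6%, 12%, 23% at 124. For all items in all countries, it is 19%, 63%, 90% at 204 and 13%, 42%, 75% at 124.

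**A shift common to all items.** Suppose one country's whole score is displaced by d scale SD, as a response style would do. The noncentrality is 300·d²·(8/9): 2.67, 10.67 and 24 for d = 0.1, 0.2 and 0.3. Rejection is 16%, 62% and 96%.

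**The case against.** The strongest objection is that the criticised test is not written down. Section 7.1 names neither country nor language, and Table 1 gives response formats without saying how scores are formed. A reader might infer that the plan prescribes an ANOVA of raw country means and that this test will reject because of translation. The documents do not support that. The comparison is a close inference from the objective and the only methods named for it, and the size of any shift is unknown. With no shift the error rate is 5%.

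Second, this is a condensed article that says its analysis plan will evolve, and psychometric checks are often left to a fuller plan. That limits the point: it cannot be said that the study omits such a check. What remains is that the article does list its checks for all analyses and does describe its cross-language safeguards, and neither covers comparability of scores.

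Third, exposure may be limited. Only measures without a validated version are translated, and the article does not say whether the willingness scale is one of them. Shifts on a few items at s = 0.1 barely raise the error rate (9%). Both facts stand and are the reason for showing a range.

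Finally, a reader might take cultural differences to be the study's main aim. They are part of one secondary objective. The primary objective concerns the experience of caregiving, motivations and what influences them.

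**Conclusion.** The concern holds in a conditional form. The plan has an explicit cross-cultural objective, names only observed-score methods for the scales concerned, and lists assumption checks and translation safeguards that do not test comparability across languages. If country means are compared on these scores, a difference could not by itself be attributed to willingness or motivation. At the planned 300 per country, rejection under equal true willingness runs from 5% with no shift, through 9% to 51% when 3 of 10 items shift in seven countries, to 27% to 96% when all 10 shift in all nine. These figures rest on an assumed loading of 0.7, a 10-item score and assumed shift SDs of 0.1 to 0.3; none is given in the documents. They illustrate the mechanism and do not predict this study's error rate.

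**What to change.** Add to section 7.1:

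1. Before any between-country comparison of a multi-item scale, measurement invariance across countries is assessed on the item data, by multi-group confirmatory factor analysis (configural, metric, scalar) or by alignment.
2. Country differences are estimated on latent means, under partial invariance or alignment.
3. Where comparability is not supported, the observed-score country difference is reported as descriptive, with an explicit caveat that it may reflect the instrument, and conclusions rest on within-country associations.
4. The report states that a response style shifting all items equally is not detected by invariance testing, because it is absorbed into the latent mean.

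No new data are needed. The costs are extra analysis work, slightly wider intervals for latent means, and weaker conclusions on country differences for some scales. Full scalar invariance over nine groups is a demanding standard, so step 3 keeps the comparison in the report and does not bar it.

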### 7.2. Module 4 Plan Analysis

Descriptive analyses will be conducted with sociodemographic and caregiving situation data to summarise sample characteristics, informal care costs and the use of paid home care services.

Informal care costs including employment-related costs, caregiver-time costs, and out-of-pocket expenses will be estimated. Unlike out-of-pocket costs, time- and employment-related costs are not measured in monetary terms and, therefore, should be valued. Time costs will be valued by two methods: the opportunity costs and the proxy good (following the recommendation in van den Berg et al. [65]). Additionally, employment-related costs will be valued using the human capital approach. Additional informal caregivers, the underlying level of dependency (i.e., need) of, and distance to, the care recipient may mediate the time and burden perceived. During analyses these interactions will be explored. Furthermore, multivariate regression analysis will be performed to find the determinants of informal care costs, e.g., those mentioned above, the demographic and socioeconomic characteristics of both the caregiver and care recipient, as well as the use of national or local formal care and support services.

The impact of the hiring of paid care workers (alongside other factors) on the amount of informal care will be examined using bivariate and linear regression. Furthermore, binary logistic regression will be used to calculate the predictors (including the hiring of paid care workers) of not having a low level of subjective wellbeing (score of 50 or over on the WHO-5 index). Finally, hours of personal care, household activities, and practical support by informal caregivers and paid care workers will be cross tabulated with each other to determine if care tasks are provided by both informal caregivers and paid care workers, only provided by paid care workers or informal caregivers, or provided by neither.

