**Module 4**							
The influence of informal care on employment and the associated costs.	Seven self-reported items address the influences of informal care on the employment situation of the caregiver, and the associated costs of this.	Categorical and numerical answers	IV, DV	✔	✔	✘	✘
Types of home care services provided by paid care workers	Eighteen (18) items assess which tasks and how many hours of care tasks (total and per type of care task) are provided by paid home care workers	Categorical and numerical answers.	IV, DV	✔	✔	✘	✘
Rationale for hiring of paid care workers	Twenty two (22) items assess the rationale for hiring paid home care workers and the decision to hire or not hire migrant care workers	Categorical answers, with each item treated separately	DV	✔	✔	✔	✔
Out-of-pocket expenses incurred by caregivers as a result of their caregiving role.	Twenty five (25) items measure out-of-pocket costs for caregivers (both in terms of overall total and per type of cost). These costs include expenditure on, e.g., caregiving support services, medical care, food, travel, home care services, aids, appliances and home modifications due to care recipient’s condition.	Categorical and numerical answers.	IV, DV	✔	✔	✘	✘
Care benefits received by the care recipient	Four self-reported items measure care benefits received (both in terms of overall total and per type of care benefit), e.g., tax benefits, cash benefits, care vouchers.	Categorical and numerical answers.	IV, DV	✘	✘	✔	✔
Self-reported questionnaire on the use of, and the out-of-pocket expenses for, care services, as well as assistive devices and aids used by the care recipient.	Twenty two (22) items detail which types of support services the care recipient receives in relation to their care and the out of pocket expenses spent in relation to their care.	Categorical and numerical answers	IV, DV	✘	✘	✔	✔

*Legend:* CG = caregiver; CR = care recipient; IV = independent variable; DV = dependent variable; Mo = moderator; Me = mediator.

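### The Module 4 cost regression has formal service use as a predictor while its outcome may contain the caregiver's payments for those services, which biases that coefficient upward wherever caregivers pay

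*Protocol article*

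**What the plan says.** Four statements in the protocol article bear on the point.

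- **Outcome.** Section 7.2 defines the cost by three components: "Informal care costs including employment-related costs, caregiver-time costs, and out-of-pocket expenses will be estimated".
- **Content of the out-of-pocket component.** In Table 1, Module 4, the caregiver measure is described thus: "These costs include expenditure on, e.g., caregiving support services, medical care, food, travel, home care services, aids, appliances and home modifications". The same row says how it is collected: "Twenty five (25) items measure out-of-pocket costs for caregivers (both in terms of overall total and per type of cost".
- **Model and predictor.** Section 7.2 plans that "multivariate regression analysis will be performed to find the determinants of informal care costs". The listed determinants include caregiver and care recipient characteristics, "as well as the use of national or local formal care and support services".
- **Objective.** Section 1.2 asks for patterns and country differences in informal care costs and, alongside them, for "the preferences for, and use of, formal versus informal caregiving".

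Nothing in the article removes service payments from the outcome of this regression, and nothing says that the three cost components will be modelled separately.

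**The concern.** Home care bought from a provider is formal care. If a caregiver buys it, the payment enters the outcome through out-of-pocket expenses, and the purchase can also enter the predictor as service use. Part of the association is then bookkeeping: users have a bill that non-users do not have.

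Two results are exposed. The first is the coefficient for formal service use in the determinants model. A reader will take it to show whether formal care goes with a lighter or heavier informal care burden, yet it adds any change in informal time and employment loss to the price of the service. The second is the country comparison. The countries were chosen partly because their care systems differ, so the share of formal care paid by caregivers may differ too. A country where families pay could show higher informal care costs for that reason alone.

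**Working it through.** The article states no cost figure, so there is none to reproduce. The check is a decomposition, followed by an illustration with assumed values.

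**Decomposition.** Write the outcome as

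cost = time + employment + other out-of-pocket + payments for formal services.

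Least-squares coefficients are linear in the outcome. With the same predictors, the coefficient for formal service use in the total-cost model is therefore the sum of its coefficients in the four component models. In a plain comparison of users with non-users, the fourth term is

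b_pay = π × m,

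where π is the share of users whose caregiver pays and m is the mean payment per payer. For services counted in the predictor, non-users pay nothing, so b_pay is zero or positive. (This assumes a linear model on the cost scale; with a log link the sum is not exact.)

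**Size, all values assumed.** Take m = 200 units and true effects of service use on time cost of 0, -100 and -300, with no effect on employment or other out-of-pocket cost. The total-cost coefficient is true effect + π × 200. Results of a simulation of 200,000 caregivers are in brackets.

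| Paying share π | b_pay | True effect 0 | True effect -100 | True effect -300 |
|---|---|---|---|---|
| 0 | 0 | 0 (-1.1) | -100 (-99.7) | -300 (-300.0) |
| 0.25 | 50 | 50 (53.5) | -50 (-50.3) | -250 (-252.7) |
| 0.5 | 100 | 100 (101.4) | 0 (2.1) | -200 (-202.8) |
| 1.0 | 200 | 200 (202.3) | 100 (100.8) | -100 (-98.9) |

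With a true effect of -100 the sign turns at π = 100/200 = 0.5. With -300 it never turns, although the coefficient is still too high by π × 200. With service payments left out of the outcome, the four simulated values in the -100 column become -99.7, -100.3, -98.0 and -99.2, so the paying share no longer matters.

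**The same in hours.** Per formal hour used, the coefficient is q × p_f - s × p_i, where q is the share of the price paid by the caregiver, p_f the service price, s the informal hours displaced and p_i the value of an informal hour. Suppose 5 hours are bought at 20 and paid in full, and displace 3 informal hours valued at 15. The result is 5 × 20 - 3 × 15 = 100 - 45 = +55, although the time cost fell by 45. Under the proxy good method p_i may be close to p_f; setting both to p gives p × (q - s). With q = 0 the payment term vanishes.

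**Country means.** The payment term adds (share using services) × π × m to a country's mean cost. With 40% using services and m = 200 (assumed), this is 0.4 × 0 × 200 = 0 where no caregiver pays and 0.4 × 1 × 200 = 80 where all do. On an assumed mean of 1,000 + 300 + 100 = 1,400 for the other components, the gap is 80/1,400 = 5.7% with identical informal care.

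**The case against.** The case on the other side is substantial, and most of it limits the point without removing it.

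- **Net sign.** A reader might infer that formal care must raise the measured informal cost. The documents do not support that. Only the payment term is pushed up; the net coefficient can be negative, zero or positive, as the table shows.
- **Overlap.** A reader might also infer that every purchase sits on both sides of the model. The predictor is worded as national or local services, which can be read as public or community provision, possibly free to the caregiver. Spending reported by the care recipient is a separate care recipient measure in Table 1. The overlap is thus partial and of unknown extent, and it vanishes where the service is free or the recipient pays.
- **Substitution.** It is tempting to say that the plan gets the substitution question wrong. It does not: Section 7.2 has a separate regression of the amount of informal care on the hiring of paid workers, and a cross-tabulation of hours by task. Neither outcome contains spending.
- **Perspective.** Table 1 describes the expenses as arising from the caregiving role. As a total of what the caregiver bears, counting bought help is legitimate. What does not follow is that this total suits a model in which use of the same services is a predictor, or a comparison that sets informal against formal care.
- **Detail left out of an article.** The full plan may model the components separately, and the text does not rule that out. But the article does state the outcome, its components and the predictor, and taken together they create the overlap.

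**Conclusion.** The point holds in limited form. As written, the determinants regression allows caregiver payments for formal services into an outcome for which formal service use is a predictor. Where caregivers pay, the coefficient is too high by the paying share times the mean payment, if read as the relation of formal care to informal care burden. Country comparisons of informal care costs pick up part of the same term. The size and the net sign depend on the paying share, the payments and the overlap between predictor and paid services. The documents give none of these, so every figure above is an illustration.

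This concerns one covariate in one regression and one descriptive comparison, under one of five secondary objectives. No data collection is compromised. It should be fixed, but it is not critical.

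**What to change.** In Section 7.2:

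1. Keep the caregiver-borne total as a descriptive cost if wanted, but show caregiver-paid formal care (home care and caregiving support services) as its own line in the totals and in the country comparison.
2. Run the determinants model by component: time cost, employment-related cost, and out-of-pocket cost without payments for home care and support services. No outcome should then contain payments for services whose use is a predictor.
3. State which services the formal care predictor covers, so that the exclusion in step 2 can be matched to it.

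Expenses are already collected by type of cost, so this needs recoding and about one paragraph of text, with no new data. The price is a few more models to report and smaller informal care cost totals.
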